## 1.d. Outcome Measures

### 1.d.1. Primary Outcome

The primary clinical outcome measure will be the presence or absence of a clinical response, defined as a 30% or greater reduction in total CAPS (past week symptom status) score from baseline to four weeks.

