### 1.d.3. Descriptive Outcomes

The impact of mifepristone on other clinical parameters will be described, including the three PTSD symptom sub-scales from the CAPS (intrusion/re-experiencing, avoidance/emotional numbing, and hyperarousal), depression (Beck Depression Inventory (BDI)), PTSD (PTSD Checklist (PCL)), sleep quality (Pittsburgh Sleep Quality Index (PSQI)), anger (State-Trait Anger Expression Inventory (STAXI)) and functional impairment (functional impairment measure (item 24) on the CAPS). The neuroendocrine effect of mifepristone in PTSD will be assessed by measuring the changes in plasma cortisol and ACTH levels from baseline to immediately after one week of treatment and from baseline to four weeks. The relationship of plasma cortisol and ACTH levels to clinical response will also be explored. As an additional descriptive measure, plasma levels of mifepristone and its metabolites will be assessed immediately after one week of treatment, and its relationship to clinical response and the trajectories of CAPS scores will be assessed.

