##### 4.n.2. *Sample size determination*

As mentioned above, the sample size has been calculated to provide at least 90% probability that mifepristone 600 mg has been correctly identified as being superior to placebo if the population difference in response rate is at least 15%. Using the calculations provided by Simon et al. (1985) and accounting for a 20% attrition rate which has been reported in other drug studies using a similar population (Bartzokis et al., 2005), a total sample size of 90 is required, or 45 per treatment group. Since the sample size varies according to the responder rate (as well as the magnitude of the difference of interest), and the responder rate for placebo is unknown, we assume a placebo responder rate of 40%, which is at the high end of the studies referenced above. By contrast, in order to have a one-sided Type I error rate of 5% and 80% power to detect the 15% difference between two

groups using a traditional hypothesis testing framework, the study would require 274~344 participants when the placebo responder rate changes from 20% to 44%, after adjustment for a 20% withdrawal rate. If the true population difference in response rate is smaller than 15% (between 10~12%) and if we still consider it clinical significant, the proposed sample size (n=72 completers or 90 with 20% withdrawal rate) will still provide at least 80~85% probability of correctly identifying the superior group.

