- a. Descriptive statistics for the change in score from baseline to one month on the STAXI and confidence intervals will be provided for each treatment group.
- b. Change in score from baseline to one month on the STAXI will be compared between mifepristone and placebo using two-sample t-test (or Wilcoxon rank-sum test if the normality assumption does not hold).
6. Functional Impairment
- a. Descriptive statistics for the change in score from baseline to one month on the functional impairment measure (item 24) from the CAPS and confidence intervals will be provided for each treatment group.
- b. Change in score from baseline to one month on the functional impairment measure (item 24) from the CAPS will be compared between mifepristone and placebo using two-sample t-test (or Wilcoxon rank-sum test if the normality assumption does not hold).
7. Neuroendocrine
- a. Descriptive statistics for the change in score from baseline to one week following treatment, and baseline to one month and confidence intervals for plasma cortisol and ACTH levels will be provided for each treatment group.
- b. Change in plasma cortisol and ACTH levels from baseline to one week following treatment and baseline to one month will be compared between mifepristone and placebo using two-sample t-test (or Wilcoxon rank-sum test if the normality assumption does not hold).
- c. Mean plasma cortisol levels at one month will be compared between clinical responders (30% reduction in CAPS score) and non-responders using a t-test (or Wilcoxon rank-sum test if the normality assumption does not hold). This analysis will be limited to those on mifepristone only.
- d. Mean ACTH levels at one month will be compared between clinical responders (30% reduction in CAPS score) and non-responders using a t-test (or Wilcoxon rank-sum test if the normality assumption does not hold). This analysis will be limited to those on mifepristone only.
8. Mifepristone and its metabolites
- a. Descriptive statistics and confidence intervals for one week following treatment for plasma levels of mifepristone and its metabolites will be provided.
- b. Mean plasma levels of mifepristone and its metabolites at one week will also be compared between clinical responders (30% reduction in CAPS score) and non-responders using a t-test (or Wilcoxon rank-sum test if the normality assumption does not hold).

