- c. A continuous mixed-effects model for longitudinal observations of CAPS scores will also be used adjusting for aforementioned baseline characteristics, indicator variable that contrasts

mifepristone vs. placebo, and plasma levels of mifepristone and its metabolites at one week to determine the effect of them on CAPS scores trajectories.

Although it is not listed as an outcome, the percentage of unique participants with concurrent psychotropic medication use change by 1 month and by 3 month (end of the trial) will be compared between mifepristone and placebo using chi-square tests. Concurrent psychotropic medication change is defined as seeking a rescue medication for those who are not on concurrent psychotropic medication prior to randomization, or seek a new psychotropic medication or require a dose increase for those on a stabilized regimen treating PTSD prior to randomization. Those analyses will also be based on mITT principle. Except the primary analysis of the primary outcome, all efficacy and safety analyses will be performed with a significance level of 5% for two-sided tests. Due to exploratory nature of the study, and the sample size was not powered on hypothesis testing framework, careful consideration is necessary when interpreting the significance of these results on the primary, secondary and descriptive outcomes. The results of the trial are considered to be hypothesis generating and are not to obtain definitive efficacy information. No adjustments for multiplicity on various secondary outcome measures are planned in this phase IIa trial. The lack of adjustment will be noted in the resulting manuscripts.

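### Cortisol and ACTH are related to clinical outcome only through a 30% CAPS cut within the mifepristone arm; adding a continuous-CAPS analysis would be a cheap gain in precision

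*Protocol*

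**What the plan says.** Protocol section 4.p.1, Descriptive Outcomes, item 7 (Neuroendocrine), fixes two analyses of hormone level against outcome.

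- Item 7c: "Mean plasma cortisol levels at one month will be compared between clinical responders (30% reduction in CAPS score) and non-responders using a t-test", with a Wilcoxon test as fallback.
- Item 7d: "Mean ACTH levels at one month will be compared between clinical responders (30% reduction in CAPS score) and non-responders using a t-test", with the same fallback.
- Each carries the restriction "This analysis will be limited to those on mifepristone only".

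The grouping variable is the primary-endpoint responder definition (section 1.d.1): "defined as a 30% or greater reduction in total CAPS (past week symptom status) score from baseline to four weeks". The stated aim in section 1.d.3 is "The relationship of plasma cortisol and ACTH levels to clinical response will also be explored". Section 4.k puts it more loosely, as the relation of the neuroendocrine response to treatment outcome.

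The rest of item 7 does not relate hormones to outcome: 7a is descriptive and 7b compares the arms. Item 8 treats plasma mifepristone more fully. Item 8b uses the same responder split, and item 8c then adds: "A continuous mixed-effects model for longitudinal observations of CAPS scores will also be used adjusting for aforementioned baseline characteristics". Cortisol and ACTH have no counterpart to 8c.

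On numbers, section 4.n.2 says "a total sample size of 90 is required, or 45 per treatment group" and refers to "the proposed sample size (n=72 completers or 90 with 20% withdrawal rate", which gives 36 completers per arm.

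**The concern.** The protocol supports the 30% cut for the primary endpoint by its use in other PTSD drug trials. It gives no separate reason for using the cut as the sole outcome scale in a within-arm hormone analysis.

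On that scale a man with a 31% reduction counts the same as one with 80%, and differently from one with 29%. With 36 men and 55% responders, the comparison is between groups of about 20 and 16 (36 × 0.55 = 19.8; 36 × 0.45 = 16.2).

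The trial's rationale is that recalibrating the HPA axis produces clinical benefit, and 7c and 7d are the only planned analyses that set cortisol and ACTH beside clinical outcome. If the relation is graded, a small within-arm analysis gives up about a third of its information. It also yields no estimate of how many CAPS points go with a given difference in hormone level.

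**Working it through.** **Inputs.** Protocol 4.n.1 and 4.n.2: 45 randomised and 36 completers per arm; placebo response 40%; relevant difference 15 points, hence 55% responders on mifepristone. Section 4.p.1: two-sided 5% for these tests. The hormone-CAPS correlation (rho) is not given anywhere in the document, so it is an assumption and a range is shown.

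**The plan's own figure.** The protocol states no power for 7c or 7d. Its sample size does reproduce. With 36 per arm at 40% versus 55%, the probability of correct selection by normal approximation is

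Φ(0.15 / √[(0.40 × 0.60 + 0.55 × 0.45)/36]) = Φ(0.15/0.1164) = Φ(1.289) = 0.901,

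and 72/0.80 = 90. The arm sizes and the 55% are therefore sound inputs.

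**Information kept by the cut.** For a normally distributed CAPS change split so that a proportion p respond, the efficiency relative to the continuous scale is φ(z_p)² / [p(1 − p)].

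- p = 0.55: z = 0.126, φ = 0.396, so 0.1567/0.2475 = 0.633.
- p = 0.40 or 0.60: 0.622.
- p = 0.30 or 0.70: 0.576.

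At 55% responders the loss is about 37%, and 0.633 × 36 = 22.8, or about 23 men. This ratio does not depend on rho.

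**Power.** Simulation with bivariate normal hormone level and CAPS change, n = 36, 55% responders, two-sided 5%. A Pearson test on continuous CAPS change is compared with the t-test of hormone level by responder status.

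| rho | Continuous | Responder t-test | Points lost (rounded) |
|---|---|---|---|
| 0.1 | 8.5% | 7.2% | 1 |
| 0.2 | 21.5% | 15.3% | 6 |
| 0.3 | 43.7% | 29.8% | 14 |
| 0.4 | 69.7% | 49.0% | 21 |
| 0.5 | 89.4% | 70.6% | 19 |
| 0.6 | 98.2% | 87.8% | 10 |

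With all 45 men, the loss is about 17 points at rho 0.3, 21 at 0.4 and 15 at 0.5. With 30% responders and n = 36 it reaches about 26 points at rho 0.45.

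**When the assumed shape is wrong.** Suppose hormone level differs by a 0.7 SD step between responders and non-responders and is otherwise unrelated to CAPS change. At n = 36 and 55% responders the planned t-test then has about 52% power, against about 35% for the correlation test. The ranking reverses.

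**The case against.** The strongest reply is that the planned test answers the question as posed. Section 1.d.3 asks about the relation to clinical response, and section 1.d.1 defines clinical response by the 30% cut. Comparing hormone levels between responders and non-responders is the literal analysis of that aim. This stands. A reader might infer that the responder comparison is a mistake or contradicts the protocol's aims; the documents do not support that, and the comparison should remain.

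Second, no decision rests on 7c or 7d. Section 4.p.1 calls the results hypothesis generating and says the sample was not sized for hypothesis tests; the go/no-go signal is the responder-rate difference. This also stands, and it keeps the severity low.

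Third, a reader might take 14 to 21 points as the plain cost of the cut. That range applies only for correlations of about 0.3 to 0.5, under a linear, bivariate-normal relation, and the protocol gives no correlation. At 0.1 the loss is about 1 point. At 0.2 both analyses miss the relation roughly four times in five. Under the step alternative the planned test is the better one, so the continuous analysis is not uniformly superior.

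Fourth, the power figures are for a Pearson test on CAPS change. They are not for the baseline-adjusted regression or the Spearman fallback proposed below, whose power was not computed. Item 8c is also a longitudinal model with a treatment indicator, so it is a precedent for using continuous CAPS and not an exact template.

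What remains is that the protocol itself fixes the cut as the only outcome scale for these two hormones, while giving plasma mifepristone both scales.

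**Conclusion.** The point holds as a cheap improvement of low severity. Items 7c and 7d relate cortisol and ACTH to outcome only through the responder cut, in about 36 men (45 at most).

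If the relation is roughly linear and normal and about 55% respond, the cut keeps about 63% of the information. The power this costs depends on a correlation that the documents do not supply: from about 1 point at rho 0.1 to about 21 at rho 0.4, falling to 10 at rho 0.6. The information loss changes little for responder rates between 40% and 60%.

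The primary decision rule and the other planned analyses are unaffected.

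**What to change.** Keep the responder versus non-responder comparison in items 7c and 7d. Add to each a linear regression, within the mifepristone arm, of week-4 CAPS total score (past week) on the hormone measure, adjusted for baseline CAPS. Report the slope with its 95% confidence interval. If normality fails, report a Spearman correlation of the hormone measure with percent CAPS change.

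Cost: about one sentence per item. CAPS and both hormones are already collected at baseline and week 4, so no new data, visits or patients are needed. The price is one further exploratory analysis per hormone with no multiplicity adjustment, in line with section 4.p.1, which plans none for secondary outcomes. The added analysis would be less sensitive than the responder test if the true relation is a step at the response threshold, which is a further reason to report both.

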#### 4.i. Safety Monitoring

Steps taken to minimize risk include excluding veterans with major medical illnesses including adrenal insufficiency, diabetes mellitus, and a history of severe TBI. The initial health assessment will consist of a medical history and physical examination with measurement of vital signs, weight, height, and laboratory testing (complete blood cell count, fasting glucose, electrolytes, magnesium, morning cortisol, creatinine, thyroid stimulating hormone, liver function tests, lipid profile, urinalysis, and ECG). For clinical safety monitoring during the trial, complete blood cell count, fasting glucose, electrolytes, and vital signs will be measured during the 3 day follow-up and one week follow-up visits. At day 3, blood will also be collected for cortisol and stored frozen for subsequent analysis at the Core Lab, located at the James J. Peter's VA Medical Center. The day 3 cortisol sample will be analyzed in the same manner as the day 7 sample, in batches, after the participant completes all study procedures. In the event of a significant AE or SAE, a blood sample will be submitted to the local medical lab for cortisol determination, if deemed necessary by the Medical Monitoring Committee and confirmed by the Study Chair. At one week follow-up blood will also be drawn for plasma levels of mifepristone and its metabolites. Although previous studies have not found that one week of mifepristone is associated with adrenal insufficiency, because there is a theoretical risk of this, participants will be monitored for this possible adverse effect. Participants will be specifically assessed for the presence of signs or symptoms of adrenal insufficiency (malaise, fatigue, vomiting, nausea, orthostasis, hyperkalemia, hyponatremia, and eosinophilia) at baseline and at follow-up visits. All investigators will grade adverse events using version 4 of

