#### Descriptive Outcomes:

Descriptive statistics and confidence intervals for the change from baseline to one month follow-up and to three month follow-up for each of the two treatment groups will be provided for each of the descriptive outcome measures. Additionally, comparisons between mifepristone and placebo will be performed; however, lack of statistical significance should not be construed as evidence of no clinical effect given the small sample size. All efficacy analyses on descriptive outcomes will be performed based on a mITT principle.

1. PTSD Symptom Sub-Scales
  - a. Descriptive statistics for the change in score from baseline to one month on the three PTSD symptom sub-scales (intrusions, hyperarousal, and avoidance) and confidence intervals will be provided for each treatment group.
  - b. Change in score from baseline to one month on the three PTSD symptom sub-scales (intrusions, hyperarousal, and avoidance) will be compared between mifepristone and placebo using two-sample t-test (or Wilcoxon rank-sum test if the normality assumption does not hold).
2. Depression
  - a. Descriptive statistics for the change in score from baseline to one month on the Beck Depression Inventory (BDI) and confidence intervals will be provided for each treatment group.
  - b. Change in score from baseline to one month on the Beck Depression Inventory (BDI) will be compared between mifepristone and placebo using two-sample t-test (or Wilcoxon rank-sum test if the normality assumption does not hold).
3. PTSD Symptom Severity

- a. Descriptive statistics for the change in score from baseline to one month on the PTSD Checklist (PCL) and confidence intervals will be provided for each treatment group.
- b. Change in score from baseline to one month on the PTSD Checklist (PCL) will be compared between mifepristone and placebo using two-sample t-test (or Wilcoxon rank-sum test if the normality assumption does not hold).
4. Sleep Quality
- a. Descriptive statistics for the change in score from baseline to one month on the Pittsburgh Sleep Quality Index (PSQI) and confidence intervals will be provided for each treatment group.
- b. Change in score from baseline to one month on the Pittsburgh Sleep Quality Index (PSQI) will be compared between mifepristone and placebo using two-sample t-test (or Wilcoxon rank-sum test if the normality assumption does not hold).
5. Anger

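### Item 8b compares plasma mifepristone between responders and non-responders without the mifepristone-only limit set in items 7c and 7d, so read literally it pools the arms and confounds level with treatment

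*Protocol*

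**What the plan says.** Section 1.d.3 makes the plasma level an exposure-response question: "its relationship to clinical response and the trajectories of CAPS scores will be assessed". Section 4.p.1, Descriptive Outcomes, carries this out in item 8.

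- Item 8b: "Mean plasma levels of mifepristone and its metabolites at one week will also be compared between clinical responders" and non-responders, by t-test or Wilcoxon test. No arm is named.
- Items 7c and 7d have the same form for cortisol and ACTH, and each adds: "This analysis will be limited to those on mifepristone only".
- The default for the section is: "All efficacy analyses on descriptive outcomes will be performed based on a mITT principle". The mITT set in 4.p.1 covers both randomized arms.
- Item 8c, a mixed model for CAPS scores, includes an indicator for "mifepristone vs. placebo, and plasma levels of mifepristone and its metabolites at one week". Both arms are therefore in that model, and arm is adjusted for.
- Sampling is not limited to one arm. Section 4.i says: "At one week follow-up blood will also be drawn for plasma levels of mifepristone and its metabolites". Table 2 schedules the same draw for all participants, as the blind would require.
- All tests other than the primary analysis use a "significance level of 5% for two-sided tests".

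**The concern.** Placebo participants take no mifepristone. If they enter 8b with levels at or near zero, the pooled comparison partly asks which arm the responders came from. When the drug works, responders are enriched for active participants and so have a higher mean level, whether or not level matters among those who took the drug. Mifepristone and its metabolites would all share this arm mix, so agreement across them would not be corroboration.

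What is at stake is the reading of exposure-response. Section 2.a.3 cites a relation between plasma level and response in psychotic depression, notes that only about one-third of participants reached the level judged optimal there, and commits the trial to examining post-treatment levels against response. The distortion grows with the treatment effect, so it is largest in the case where the level result would be used to plan a Phase III trial.

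**Working it through.** **Inputs from the protocol.** Section 4.n.2: "we assume a placebo responder rate of 40" per cent; a difference of 15 points, hence 55% on mifepristone; 45 randomized and 36 completing per arm. Section 4.n.1: placebo response of 20% to 44% across the cited trials, and a largest contrast of 67% vs 37% (a paroxetine trial). Test level: 5%, two-sided.

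**Assumptions, not in the protocol.** Placebo level is zero. Active-arm levels are lognormal with one-third above 1800 ng/ml (the threshold is quoted in 2.a.1 and the one-third in 2.a.3; both are used only for scale). The coefficient of variation (CV) is 0.4, varied from 0.2 to 0.7. Within each arm, response is independent of level, so there is no true concentration-response relation.

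**The plan's own figure.** The exact binomial probability that the better arm shows the higher rate, at 36 per arm and 55% vs 40% with ties split equally, is 0.899. This agrees with the stated 90% and confirms the planning inputs.

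**Expected pooled difference.** With response rates p1 (mifepristone) and p0 (placebo), equal arms and active-arm mean level m:

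difference = m × [p1/(p0 + p1) − (1 − p1)/(2 − p0 − p1)]

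At 55% vs 40%:

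- share of responders on active drug: 0.55/0.95 = 0.579
- share of non-responders on active drug: 0.45/1.05 = 0.429
- difference: 0.150 × m, about 247 ng/ml if m = 1,642 ng/ml (the mean at CV 0.4)

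The 15% needs no assumption about the shape of the level distribution. It is zero only when p1 = p0. Within the active arm alone the expected difference is zero.

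**Rejection rates with no true relation** (6,000 simulated trials per row):

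| Placebo vs mifepristone response | Per arm | CV | Pooled: t / Wilcoxon | Active arm only: t / Wilcoxon |
|---|---|---|---|---|
| 40% vs 40% | 36 | 0.4 | 4.5% / 4.4% | 4.7% / 4.5% |
| 40% vs 55% | 36 | 0.4 | 20.2% / 21.2% | 5.2% / 5.2% |
| 40% vs 55% | 36 | 0.2 | 24.0% / 21.9% | 4.6% / 4.4% |
| 40% vs 55% | 36 | 0.7 | 16.2% / 22.5% | 4.2% / 4.4% |
| 40% vs 55% | 45 | 0.4 | 23.1% / 25.0% | 4.9% / 5.3% |
| 20% vs 35% | 36 | 0.4 | 25.1% / 26.6% | 4.7% / 4.4% |
| 44% vs 59% | 36 | 0.4 | 19.9% / 20.9% | 5.0% / 4.8% |
| 37% vs 67% | 36 | 0.4 | 62.0% / 66.6% | 5.2% / 5.3% |

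The first row shows that pooling is harmless without a treatment effect, so the inflation comes from that effect. With half the pooled values at zero, normality would not hold, and 8b's own rule would lead to the Wilcoxon figure.

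**The case against.** The best reply is that nobody meant to pool. Items 1a to 7a promise descriptive statistics by treatment group; 8a drops that phrase, perhaps because only one group has levels to describe, and 8b carries on from 8a. Items 7c and 7d had to name the arm because cortisol and ACTH are measurable in everyone; for drug levels an author may have thought it self-evident. The protocol does not say that placebo values are set to zero. Table 2 and the Laboratory Evaluations section describe collection and assay without naming an arm, but neither defines an analysis set. The statistical analysis plan, not available here, may restrict 8b.

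This stands as far as intent goes: a reader might infer that the protocol deliberately pools, and the text does not establish that. It does not clear the wording. The section default covers both arms, 8c shows that both arms enter a level analysis in the same item, and nothing in the protocol restricts 8b.

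Two further inferences should be resisted. One is that any treatment effect will produce a false significant relation: the shift in the expected difference follows from pooling, but at the design effect about 75% to 80% of trials would show nothing significant. The other is that the 62% to 67% rates are to be expected: they need a 30-point difference, twice the planning value.

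The consequence is also limited. Item 8c separates arm from level, though for CAPS trajectories and not for responder status, and the protocol calls its results hypothesis generating and urges care in interpreting significance.

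**Conclusion.** The point holds as a defect of wording with a measurable effect if 8b is followed literally. A pooled 8b carries a spurious expected difference of about 15% of the active-arm mean at 55% vs 40%, and rejects in roughly 20% to 25% of trials at 36 to 45 per arm where 5% is intended. Over the assumed CVs of 0.2 to 0.7 at 36 per arm, the range is 16% to 24% for the t-test and 21% to 23% for the Wilcoxon test. Limited to the active arm, rejection stays at 4% to 5%.

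The 15% rests on placebo levels at or near zero and on the planning response rates; the rejection rates rest also on the assumed level distribution. The matter is modest in weight: one descriptive analysis, with no bearing on the 15-point primary decision rule, the sample size or data collection. It is still worth correcting, because a wrong exposure-response hypothesis is a poor product for a hypothesis-generating trial.

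**What to change.** Add to item 8b the sentence already used in 7c and 7d: "This analysis will be limited to those on mifepristone only". If the statistical analysis plan already restricts 8b, bring the protocol into line with it. Item 8c can keep both arms, since it carries the treatment indicator. The cost is one sentence; no participants, samples or data collection are affected.
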